### Biases

To reduce confounding and other sources of bias affecting observational data, we will adopt a Target Trial Emulation (TTE) framework (
Hernán *et al.,* 2022). TTE enables observational data to be mapped to a hypothetical target experimental trial counterpart by creating the specification of an ideal (pragmatic) trial and using this as a basis to shape the observational study design. TTE consists of one, defining the specifications of a hypothetical target experimental trial of the causal question of interest (including the corresponding effect), two, emulating the specifications of the ideal target trial using observational data and three, estimating the effects of interest using the emulated trial data. The first component of TTE involves defining inclusion/exclusion criteria for entry, a treatment strategy (including time of treatment assignment), follow-up frequency and modality, outcome measures, causal contrasts of interest (estimands) and estimation methods. The second component of TTE involves handling the observational data to emulate the structure of the data that would be gathered in the specified target trial. Finally, the third component of TTE concerns dealing with the inevitable confounding that affects observational data and explicitly outlining the analytical methodology ahead of the data wrangling. In
Table 6 we describe the (ideal) target trial one would design to investigate the causal effect of SEN provision on the selected health and educational outcomes in the first year of compulsory education on CLP children and the equivalent emulated trial to be generated from ECHILD.

**Table 6. T6:** Trial emulation to estimate the causal effect of SEN by Year 1 on unplanned hospitalisations by Year 6 in children with cleft lip and/or palate (without other congenital anomalies).

	Ideal target trial	Emulated target trial
**Eligibility criteria**	Geography: England Started Year One between 2008 and 2018. Diagnosed with cleft lip and/or palate prior to Year One Born in England	Geography: England Started Year One in a state school between 2008 and 2018. Identified in HES with cleft lip and/or palate before start of Year One Has a birth record in HES Linked to NPD
**Recruitment** ** period**	Started Year 1 in between the academic years 2008/2009 and 2018/2019	Started Year One between the academic years 2008/2009 and 2018/2019
**Follow-up** ** duration**	From: Randomization to the intervention To: the end of primary school OR loss of follow-up (e.g., emigration) OR death OR end of study	From: January Census in Year One To: the end of primary school OR loss of follow-up in NPD OR death OR end of study/end of data (for HES: 31 August 2019)
**Outcome(s)**	Unplanned hospital utilisation as defined by days in AE or APC Medical related absences as defined using half-day sessions. Unauthorised absences as defined using half day sessions	Unplanned hospital utilisation as defined by days in AE or APC Medical related absences as defined using half-day sessions. Unauthorised absences as defined using half day sessions
**Interventions to** ** be compared**	One of three categories of SEN (none, SEN, EHCP) to be delivered following randomization (between start of reception and end of Year One	One of three categories of SEN (none, SEN, EHCP) as recorded by the January census in Year One
**Causal contrasts**	The average treatment effect of initiating SEN versus non-initiating SEN at all by Year One on the number of unplanned hospital days expressed as a rate ratio. The average treatment effect of initiating EHCP versus initiating SEN by Year One on the number of unplanned hospital days expressed as a rate ratio.	The average treatment effect of recording SEN versus non- initiating SEN at all by Year One on the number of unplanned hospital days expressed as a rate ratio. The average treatment effect of recording EHCP versus recording SEN by Year One on the number of unplanned hospital days expressed as a rate ratio. These estimands will be defined for the whole population and also for the sub-populations of “treated” and “untreated” children, that is the children who were (or were not) recorded to receive the relevant intervention.
**Analysis plan**	Poisson or Negative Binomial Regression (depending on the degree of overdispersion) of the number of events accountings for duration of follow-up. Clustering by school and/or local authority to be dealt with using either mixed effects models or robust inference (e.g., GEE).	Appropriate methods for confounding adjustment (such as regression adjustment and standardisation, or propensity score-based methods) involving Poisson or Negative Binomial Regression (depending on the degree of overdispersion) of the number of events accountings for duration of follow-up. Clustering by school and/or local authority to be dealt with using either mixed effects models or robust inference (e.g., GEE).

The estimands we will target are firstly, the average treatment effect (or average causal effect): this is a causal contrast of average potential outcomes for the whole isolated CLP population, secondly, the average treatment effect in the treated: this is a causal contrast restricted to the “treated”, i.e., those that received SEN and finally, the average treatment effect in the not treated; the causal contrast in those who did not receive SEN in Year One (
Wang *et al.,* 2017).

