### Dataset and linkage

The data source we propose is the ECHILD database, a pseudo-anonymised dataset that links the National Pupil Database (NPD) with Hospital Episode Statistics (HES). In brief, the ECHILD's extract of the NPD contains data from academic terms (Summer, Autumn, and Spring) between 2006 and 2020 and contains information on (but not limited to) school, local authority, year/month of birth, gender, ethnicity, first language, socioeconomic status, free school meal status, absence related data, social care/children in need related data and SEN provision.

The ECHILD’s extract of HES contains details on accident and emergency attendance, admitted patient care, critical care, and outpatient appointments between 1997 until 2021. It contains details on birth admissions, sex recorded by physician, ethnicity, clinical information recorded during hospital admissions, including details of diagnoses, and operations. HES covers 99% of public hospital activity in England (
Herbert *et al.*, 2017). HES records since 1998 are also linked to ONS Mortality data covering information on causes and timing of deaths. The linkage coverage periods are described in
Mc Grath-Lone *et al.* (2022). ECHILD has been shown to have a linkage rate between NPD and HES of 95%; the high linkage rates are attributable through a two-stage linkage process (
Libuy *et al.*, 2021).

Full methodology of creating the ECHILD dataset is described by
Mc Grath-Lone *et al.,* 2022. Enquiries to access to the ECHILD dataset is obtainable by contacting
[contact]; all researchers accessing the ECHILD dataset will need to be an Office of National Statistics (ONS) accredited researcher. Access to the ECHID dataset will be made through the ONS Secure Research Service, a trusted research environment which requires the researcher’s institution to have Assured Organizational Connectivity, Population

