Our population consists of children with isolated CLP recorded in hospital records and followed from Year One of school (the first full year of compulsory education, where pupils are five years old on the first day) between academic years 2008/2009 and 2018/2019 (i.e., born between 1 September 2003 and 31 August 2013). This period was chosen as it contains information of school readiness tests (known as Early Years Foundation Profile - a known good predictor of SEN provision) and 2018/19 was the last entry-into-school academic year prior to the COVID-19 pandemic where access to hospitals and provision of education vastly changed. To identify pupils who started Year One between 2008/2009 and 2018/2019, the earliest recording of “1” from the “NCActualYear” (National Curriculum Actual Year) variable in the NPD dataset will be used; for children whose “NCActualYear” variable is marked as empty or X, we will use “AgePartAtStartOfAcademicYear” equal to 5.

To identify pupils with isolated CLP, International Classification of Diseases version 10 (ICD-10) codes will be applied to primary and secondary HES diagnoses in any hospital admission prior to the start of compulsory education using the following codes: Q35*, Q36* and Q37*. For each pupil, the earliest recorded date in HES will be considered the “diagnosis” date. Pupils whose first recording of CLP in HES is after their first year in school will not be included as SEN allocation needs to proceed diagnosis to avoid reverse causality. Children born with further major congenital anomalies, will be identified using the EUROCAT code list (
‘EUROCAT Guide 1.5 Chapter 3.3’, 2023) and excluded using the ICD-10 codes listed in
Table 1 to reduce competing needs for SEN provision. The EUROCAT code list was used as it captures major congenital anomalies and not minor anomalies.

**Table 1. T1:** Inclusion and exclusion criteria used to define isolated cleft lip and/or palate.

Condition, by severity	ICD-10 codes *	
	Inclusion	Exclusion **

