### Follow-up

The study population will be followed-up from the initial January census in Year One (to account for time to apply for SEN) until the end of primary school (end of July of Year Six), lost to follow-up, or end of study, whichever occurred first. Children will be considered lost to follow-up if they no longer appear in any NPD school census during primary education; this could be due to a variety of reasons including, transfer to a non-state-funded school, emigration, death, or off-rolling (
Jay *et al.*, 2022).

Although ECHILD can be used to follow up children beyond the end of primary school for some academic cohorts, we will limit our follow-up period in this protocol to Year 6 for two reasons: firstly, entering secondary (or middle) education will re-evaluate the need for SEN, and many pupils may no longer be offered SEN provision, and secondly, the time between the assignment of SEN considered here and the outcome may be too long if beyond Year Six, with the outcome affected by many intermediate factors (pupils starting Year One in 2008, would have 13 years of follow-up in HES).

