Absences in the NPD are recorded termly as sessions, corresponding to half-days in school; the total number of potential sessions in a term is also provided. School absences will be measured as sessions between January of Year One and the end of follow up (maximum: end of Year Six). As the population of interest is based upon health needs, our school absences will include those related to medical need. See
Table 4 for the case definition of medically related absences during school. In addition to medically-related absences, we will separately evaluate the impact of SEN on unauthorised absences; such evaluations are needed as absenteeism is related to poor academic performance (
Allen *et al.,* 2018).

**Table 4. T4:** Determining medical related absences in the National Pupil database.

Absence Reason in NPD	Meaning	Action
C	Number of authorised sessions missed during the academic year as pupil is absent due to other authorised circumstances.	Exclude
E	Number of authorised sessions missed during the academic year as pupil is excluded, with no alternative provision made.	Exclude
F	Number of authorised sessions missed during the academic year due to agreed extended family holiday.	Exclude
G	Number of unauthorised sessions missed during the academic year as pupil is on a family holiday, not agreed, or is taking days in excess of an agreed family holiday.	Include
H	Number of authorised sessions missed during the academic year due to agreed family holiday.	Exclude
I	Number of authorised sessions missed during the academic year due to Illness (NOT medical or dental etc. appointments).	Include
M	Number of authorised sessions missed during the academic year due to medical/ dental appointments.	Include
N	Number of unauthorised sessions missed during the academic year as pupil missed sessions for a reason that has not yet been provided.	Include
O	Number of sessions missed during the academic year for an unauthorised absence not covered by any other code/description.	Include
R	Number of authorised sessions missed during the academic year due to religious observance.	Exclude
S	Number of authorised sessions missed during the academic year due to study leave.	Exclude
T	Number of authorised sessions missed during the academic year due to traveller absence.	Exclude
U	Number of unauthorised sessions missed during the academic year as pupil arrived after registers closed.	Exclude

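### Hospital follow-up has a pre-pandemic calendar stop but the absence outcomes have none, so five entry cohorts can contribute 2020 sessions

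*Protocol article*

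**What the plan says.** The population paragraph under Dataset and linkage ends recruitment with the 2018/19 cohort because "2018/19 was the last entry-into-school academic year prior to the COVID-19 pandemic where access to hospitals and provision of education vastly changed". Disrupted education is therefore one of the plan's own reasons for restricting the design.

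The Follow-up section runs every child "until the end of primary school (end of July of Year Six), lost to follow-up, or end of study, whichever occurred first". It gives no date for the end of study. Table 6, in the follow-up row for the emulated trial, adds "end of study/end of data (for HES: 31 August 2019"). That is the only calendar stop in the document.

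For absences, the Outcome variables section says: "School absences will be measured as sessions between January of Year One and the end of follow up (maximum: end of Year Six"). The Analysis section takes total sessions over the same window as the offset. Dataset and linkage says that the school extract "contains data from academic terms (Summer, Autumn, and Spring) between 2006 and 2020" and lists among its contents "absence related data, social care/children in need related data and SEN provision". The hospital extract is described as covering contacts up to and including "outpatient appointments between 1997 until 2021".

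The sensitivity analyses do not address the pandemic period.

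**The concern.** The pre-pandemic restriction acts on the year of entry, but the outcomes accrue over the following five and a half years. A child who entered in 2018/19 is in Year Two during 2019/20, and four earlier cohorts are also still in primary school then. For hospital use, the 31 August 2019 stop keeps the outcome window before the pandemic. For absences nothing in the text does so.

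Three things are at stake. If attendance or its recording in 2020 changed differently across the None, SEN Support and EHCP groups, the absence rate ratios would mix that change with the effect of Year One provision. Hospital and absence effects would cover different calendar windows within one emulated trial. And if the difference-in-difference idea around the 2014 SEN change is pursued for absence, the exposed cohorts all lie on the later side of that change.

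**Working it through.** **Inputs from the protocol.** Entry cohorts 2008/09 to 2018/19, eleven in all (Dataset and linkage; Table 5). Follow-up from the January census of Year One to July of Year Six (Follow-up). School data by term up to 2020, last term not stated (Dataset and linkage).

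**Assumptions.** Equal cohort sizes, three equal terms a year, no loss to follow-up, and disruption counted from spring term 2020. The documents give no start date for the pandemic.

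**Check against the plan's own figure.** A child starting Year One in autumn of year *c* finishes Year Six in July of *c* + 6 and was born between 1 September *c* − 6 and 31 August *c* − 5. For *c* = 2013, Year Six ends in July 2019 and births end on 31 August 2008. This agrees with the Outcome variables section, which limits Key Stage Two results to births in 2003 to 2008. Cohorts 2014/15 to 2018/19 finish later: **five of eleven**.

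**Terms per child.** Two in Year One plus 5 × 3 in Years Two to Six = 17. The six cohorts 2008/09 to 2013/14 complete all of them: 6 × 17 = 102. The five later cohorts depend on the last term held:

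| Last term held | Terms, cohorts 2014/15 to 2018/19 | Total | Terms in 2020 | Share |
|---|---|---|---|---|
| Summer 2019 | 14+11+8+5+2 = 40 | 142 | 0 | 0% |
| Spring 2020 | 16+13+10+7+4 = 50 | 152 | 5 | 5/152 = 3.3% |
| Summer 2020 | 17+14+11+8+5 = 55 | 157 | 10 | 10/157 = 6.4% |
| Autumn 2020 | 17+15+12+9+6 = 59 | 161 | 14 | 14/161 = 8.7% |

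With data to summer 2020, the share within each exposed cohort is 2/17 = 12%, 2/14 = 14%, 2/11 = 18%, 2/8 = 25% and 2/5 = 40%, the last for 2018/19.

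**Is the hospital stop forced by the data?** Not by the extract as described, which runs to 2021. The Follow-up section agrees: it counts 13 years of hospital follow-up for pupils starting in 2008, and 2008 + 13 = 2021. The reason for the August 2019 date is not given.

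**Ten or eleven cohorts.** The protocol recruits "between academic years 2008/2009 and 2018/2019 (i.e., born between 1 September 2003 and 31 August 2013"). Those birth dates span ten school years, since Year One in 2008/09 needs births from 1 September 2002. Dropping that cohort removes 17 terms, and the summer 2020 share becomes 10/140 = 7.1%. The count of exposed cohorts stays at five.

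**The case against.** The strongest reply is that the plan never says 2020 absences will be analysed. The end of study is undated, the 2020 limit describes the extract in general, and a condensed article may leave a data lock date to the full protocol. Table 6 is also titled for hospitalisations. Part of this stands: the inclusion of 2020 sessions is inferred, and a reader should not take it as stated. But Table 6 lists both absence outcomes and does fix a calendar stop, for one source only. That is a one-sided rule in the text, not just an omitted detail. Reading 31 August 2019 as the stop for everything is not supported, because the date is restricted to HES.

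A reader might also infer that the absence rate ratios are biased, or that cohort adjustment is useless here. Neither follows. Children in one academic cohort share the same planned calendar window, cohort is a listed covariate, and SEN category is fixed by January of Year One, before 2020 for every cohort. A proportional shock common to all categories is therefore dealt with by conditioning on cohort. Differential recording would bias the ratio. A true difference in the pandemic's effect by category is closer to effect modification by period.

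Nor can a size be put on the bias. Suppose one category had no absences recorded in the 2020 terms while its possible sessions still counted. A true ratio of 1.0 would then appear as 1/(1 − 0.40) = 1.67 in the 2018/19 cohort and 1/(1 − 0.064) = 1.07 pooled. This is an extreme scenario, not a bound, and nothing in the documents suggests it. If closed sessions are not counted as possible sessions, it disappears.

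The difference-in-difference analysis is only mentioned as a possibility, so it adds little weight.

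**Conclusion.** The point holds as an inconsistency in the design: the plan treats pandemic-era education as a reason to restrict entry and stops the hospital outcome before it, but sets no matching stop for absences. Five cohorts can contribute 2020 sessions to both absence outcomes if any 2020 term is held. The share is about 3% to 9% of cohort-terms, 6.4% for data to summer 2020, and zero if no 2020 term is held, under the equal-cohort and equal-term assumptions. It is concentrated in the latest cohorts.

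Bias would require attendance or recording changes that differ by SEN category. The documents neither show nor exclude these, and the pooled effect may well be modest. The change is worth making before analysis because it is cheap and no planned sensitivity analysis covers the issue.

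**What to change.** In Table 6 and the Follow-up section, state that the primary analysis of both absence outcomes ends at the end of summer term 2018/19, matching the HES stop, and that this applies to the absence sessions and to the offset. State the last school term held. Use any later terms only in a labelled sensitivity analysis.

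The text change is about one line in each place. The cost in data, if the extract runs to summer 2020, is 157 − 142 = 15 cohort-terms (9.6%). It would be 10 of 152 (6.6%) with data to spring 2020 and 19 of 161 (11.8%) with data to autumn 2020. The loss is uneven: with data to summer 2020 the 2018/19 cohort falls from five terms to two and keeps only Year One. If the authors prefer to retain the later terms in the primary analysis, they should justify the different calendar windows and report the truncated analysis beside it.

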### Analysis

**
*Explorative analyses.*
** To estimate the representativeness and external validity of the derived cohort, we will compare the following distributions against existing literature, firstly, the rates of CLP children who start Year One between 2008/09 and 2018/19 (CRANE, 2021) and secondly, previously published rates such as school academic attainment (
Fitzsimons *et al.*, 2018). 

To understand whether pupils who are recorded to have received different categories of SEN provision had the chance to be recorded with another category and therefore for the intervention levels to be comparable using the available data (i.e. to assess whether the positivity assumption could be invoked when performing casual inference (
Zhu *et al.*, 2021)), we will examine the distribution of the propensity scores for the recording of SEN support/EHCP across the subgroups of children defined by their observed characteristics. The propensity scores will be predicted using logistic regression, with the covariates mentioned above included as predictors. As there are three categories of SEN (None, SEN Support and EHCP), pairwise propensity score comparisons (
Rassen *et al.*, 2013) will be evaluated for common support between: None vs SEN Support, None vs EHCP and SEN Support vs EHCP. The robustness of the selected propensity score model would be assessed by triangulating the predicted scores with those derived using machine learning methods (such as Classification and Regression Trees) (
Lee Brian *et al.*, 2010).

**
*Causal inference.*
** Once explanatory analyses have been completed, causal inference will be conducted for pairs of interventions which have common support. To account for the distribution of our outcome, that is number of unplanned hospital contacts and number of absence sessions, we will use Poisson (or negative binomial) regression models. To account for differential follow-up time, we will use the logarithm of one of the following as offsets: days between January of Year One and end of follow-up for hospitalisation usage and total number of full sessions between January of Year One and end of follow-up for school absences. The likely clustering of pupils within local authority will be addressed either by fitting mixed effects models or by using robust inference (or both).

We will triangulate complementary estimation methods to address confounding bias due to non-random assignment of SEN provision. We will compare results obtained assuming no-unmeasured confounding (that is, we have data on all the relevant confounders) and assuming instead that we have an instrumental variable (if there is for example variation in SEN provision by local authorities). Our analyses will involve three general approaches.

The first approach will include “traditional” epidemiological methods such as reporting of crude associations (“naïve estimator”) between intervention and outcome, and of conditional associations obtained by fitting appropriate regression models (
Bender, 2009); due to the conditional nature this method, the evaluation of these effects cannot evaluate our causal contracts of interest, such as the average effect on the whole population.

The second approach will involve dealing with measured confounding using outcome-based models (
Smith *et al.*, 2022), such as the parametric g-formula, inverse probability weighting of marginal structural models, and inverse probability weighting regression adjustment. Confidence intervals for these models will be estimated using bootstrapping (1000 replicants). These estimation methods target our estimands of interest, including the average treatment effect, average treatment effect in the treated and the average treatment effect in the not treated (see above).

The third set of methods, instrumental variable analysis, will only be possible if suitable instruments for SEN provision are identified (
Greenland, 2018), for example if there are policy changes in provision that are implemented at different times across local authorities or changes in school policy for example brought about by governance change (
Liu *et al.*, 2020). There is a well-documented change in SEN provision from 2014, which may also allow a difference-in-difference approach to be implemented.

**
*Missing data.*
